#### Data collection

The data collection timeline for this phase is illustrated in Fig. 3. Data collection for Phase 3 was similar to Phase 2 with the addition of a mid-intervention, a 6-month post-intervention data collection, and additional measures collected from parents and canteen vendors.

The instruments used for quantitative measurements in Phase 3 were largely similar to those used in Phase 2, with some refinements made to the phrasing and response options in the main questionnaire. A feedback survey for parents was also developed to assess parent’s feedback on the lesson videos and home activities. An observation checklist of the canteen environment was also developed to examine the availability of healthier choices, the canteen vendor’s compliance with the Healthy Meals in School Programme guidelines [44], the interaction between canteen vendors and students, etc.

The selection of participants for the focus groups was the same as in Phase 2. Different semi-structured topic guides were developed for Phase 3 to assess the extent of students’ and teachers’ awareness and knowledge retained from the PEDAL lessons, collect feedback on the whole PEDAL intervention, and explore perspectives on behaviour change and habit formation in students. For the short interviews with canteen vendors, guiding questions were developed to explore their perspective of the school food environment and perceived changes among students after the intervention. All data collected were delinked from their personal information and replaced with a unique code.

#### Data analysis

Descriptive statistics from the quantitative data for the recruitment capability, data collection procedures, and social validity dimensions will also be presented separately for pre-intervention and post-intervention data in this phase. Pre-post intervention comparisons of the behavioural outcomes will be assessed using appropriate statistical analyses (e.g. paired *t*-test for normally distributed variables and Wilcoxon signed rank test for variables with non-parametric distributions). Pre- and post-intervention ideation scores for healthy eating and physical activity, derived from the composite of the ideation variable scores, will be compared. Regression analyses will be conducted to examine the associations between ideation scores and behavioural outcomes.

Similar to Phase 2, qualitative data from FGDs and interviews will be transcribed and analysed using applied thematic analysis [50], to answer the research questions for the social validity, practicality, implementation, and (perceived) potential effectiveness dimensions. When possible, both quantitative and qualitative data will be integrated and reported for the feasibility evaluation.

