#### Setting and participants

Upon completion of the intervention prototype, two co-educational public schools in Singapore were recruited by convenience sampling to implement components A and B (health education lessons and home activities) of PEDAL. Co-educational public schools were selected as these were the most common type of primary schools in Singapore. The participants were students from the Primary 5 level, typically aged between 10 and 11 years old, from each school. This age group was chosen based on previous research that found that children aged 10 and above were capable of independently recalling and reporting their past activities [13, 46]. Two schools were selected for the pilot test as the required sample size to establish feasibility was calculated to be 385. This was calculated using a confidence interval (CI) approach [47], with a 95% CI, a margin of error of 0.05, and an expected completion rate of 50% based on our previous experience conducting research studies in primary school. Given that a primary school typically consists of six to eight classes of 40 students per level, the recruitment of two schools will meet the required sample size calculated. As the intervention posed minimal risk and was conducted as part of the school's Physical and Health Education curriculum, all Primary 5 students in the two selected schools were eligible to participate.

Both components, A and B, were delivered by each school’s Primary 5 Physical Education (PE) teachers. Training and lesson materials (e.g. slides, videos, home activity instructions, activity booklets for students, and teacher’s guide) were provided by the research team to the PE teachers before the intervention commenced. PE teachers from each school were given 8 weeks to complete the delivery of all the lessons and activities during the weekly 30-min health education lessons. Consent was obtained from teachers for delivering the intervention and parents regarding data collection from their children. Students whose parents or guardians did not provide consent for data collection were allowed to attend the lesson but were not included in the data collection.

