#### Setting and participants

The setting, selection of schools, and participants for this pilot study followed the same procedures as Phase 2. However, two other schools were approached to participate in this study. The ideal number of participants for this phase was 385 students, following the same calculation in Phase 2.

Based on the feedback from Phase 2, more time was needed to complete the series of health education lessons in addition to the scheduled physical and health education lessons. Therefore, the schools in this pilot study were given 12 weeks to complete all the lessons and activities. Like Phase 2, consent was obtained from teachers for delivering the intervention and parents regarding data collection from their children. Students whose parents or guardians did not provide consent for data collection were allowed to attend the lesson without any data collected from them.

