## Discussion

Multiple health promotion programmes have been conducted in local public schools to improve children’s diet and movement behaviours; however, these interventions tend to be of a single component [14, 21]. With the growing body of literature demonstrating the effectiveness of multicomponent interventions, there is a need for multicomponent interventions to support healthy behaviour change among children in Singapore. However, information on the feasibility and acceptability of multicomponent interventions in Singapore is lacking. To our knowledge, this is the first study detailing the development and testing of a theory-driven multicomponent and school-based educational intervention among primary school children that targets both dietary and movement behaviours of children on the individual, interpersonal and environmental levels.

This study seeks to identify probable “active ingredients” of the intervention and understand the factors leading to a successful implementation of a multicomponent school-based intervention through the pilot testing of the PEDAL intervention. However, it should be noted that only two schools were recruited for the feasibility and pilot testing phase of the study which means that the findings may not be generalisable to all schools in Singapore or all co-educational public schools. As funding and resource constraints limited our ability to recruit more schools, only two schools underwent the intervention, and a pretest-posttest design was used. A limitation of such design is that it limits our certainty of how the outcomes might change in the absence of the intervention. Therefore, findings on the potential effectiveness should be interpreted with caution, and a larger-scale definitive trial (e.g. a randomised controlled trial (RCT)) should be conducted to assess the effectiveness of this intervention.

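### The tests named for the Phase 3 pre-post comparisons treat students' changes as independent, although lessons are taught by class in two schools; if changes correlate within classes, intervals and p-values are too favourable

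*Protocol article*

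**What the plan says.** All references are to the protocol article.

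- **Analysis.** Under Phase 3, Data analysis: "Pre-post intervention comparisons of the behavioural outcomes will be assessed using appropriate statistical analyses". The sentence then gives two examples, a paired t-test for normally distributed variables and a "Wilcoxon signed rank test for variables with non-parametric distributions". Distributional shape is the only stated basis for choosing between them. The next sentences say that ideation scores will be compared before and after, and that "Regression analyses will be conducted to examine the associations between ideation scores and behavioural outcomes".
- **Design.** The Discussion states that "only two schools underwent the intervention, and a pretest-posttest design was used".
- **Delivery.** Under Phase 2, Setting and participants, Components A and B are delivered by each school's "Primary 5 Physical Education (PE) teachers", and "a primary school typically consists of six to eight classes of 40 students per level". Phase 3 follows the same procedures in two other schools. Component D acts on the canteen and the recess breaks of a whole school level.
- **Size.** For Phase 3: "The ideal number of participants for this phase was 385 students, following the same calculation in Phase 2". That calculation was made "with a 95% CI, a margin of error of 0.05, and an expected completion rate of 50" per cent.
- **Use.** Phase 3, Key measures, says that changes in behavioural outcomes will be explored to help choose the primary outcome and to plan the power of the definitive trial.

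Clustering, an ICC, a design effect, a multilevel model and cluster-robust errors are mentioned nowhere.

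**The concern.** Classmates share a teacher, lesson dates, the fidelity of delivery and the games and discussion in class. Table 2 has goals set partly from class-level feedback, and Table 3 measures fidelity by teacher checklist and class observation, so the team itself allows for variation in delivery. Students in one class may therefore change together.

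Pairing removes stable differences in level between classes. It does not remove differences between classes in the amount of change, and these are what a paired test must allow for. If they exist, the paired t-test uses a standard error that is too small. The Wilcoxon test has no standard error as such, but its null variance is understated in the same way.

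At stake is the apparent precision of the pre-post changes in fruit and vegetable intake, MVPA, screen time and quality of life. Intervals that are too narrow can make one outcome look more responsive than the data support when the primary outcome of the next trial is chosen.

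**Working it through.** **1. The plan's own figure.** n = 1.96² × 0.5 × 0.5 / 0.05² = 384.15 (unrounded normal quantile), rounded up to 385. The figure reproduces. It is the formula for a simple random sample, with a design effect of 1, so the sample size also treats students as independent.

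**2. Inputs.**
- Classes: 6 to 8 per school × 2 schools = 12 to 16 (the article's typical figures).
- Students per class, m: 385/12 = 32.1 to 385/16 = 24.1.
- Class ICC of the change scores: not in the documents. Assumed range 0.01 to 0.10.

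**3. Formulas.** Design effect DE = 1 + (m − 1) × ICC. The standard error is too small by a factor √DE. Effective sample size = 385/DE. Actual two-sided error of a nominal 5% test = 2 × [1 − Φ(1.96/√DE)].

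Example, 12 classes, ICC 0.05: DE = 1 + 31.1 × 0.05 = 2.55; √DE = 1.60; 385/2.55 = 151; 1.96/1.60 = 1.23, giving an error of 0.22.

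**4. Results (12 classes to 16 classes).**

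| Assumed ICC | DE | SE factor | Effective n | Actual error |
|---|---|---|---|---|
| 0.01 | 1.31 to 1.23 | 1.14 to 1.11 | 294 to 313 | 8.7% to 7.7% |
| 0.02 | 1.62 to 1.46 | 1.27 to 1.21 | 237 to 263 | 12.4% to 10.5% |
| 0.05 | 2.55 to 2.15 | 1.60 to 1.47 | 151 to 179 | 22% to 18% |
| 0.10 | 4.11 to 3.31 | 2.03 to 1.82 | 94 to 116 | 33% to 28% |

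**5. Smaller analysed numbers.** At the minimum consent and completion thresholds in Table 3, a class of 40 yields 40 × 0.5 × 0.5 = 10 students. Then DE = 1.09 at ICC 0.01 and 1.45 at 0.05, and the error is 6.0% and 10.4%. The problem shrinks with m but does not vanish.

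**6. Simulation check.** Change scores with no true mean change, 14 classes of 27, 4,000 runs per ICC:

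| ICC | Paired t | Wilcoxon | t-test on class means |
|---|---|---|---|
| 0 | 4.7% | 5.0% | 5.0% |
| 0.01 | 7.5% | 7.5% | 4.5% |
| 0.02 | 11.0% | 11.0% | 5.2% |
| 0.05 | 19.2% | 18.7% | 5.0% |
| 0.10 | 29.9% | 29.0% | 4.7% |

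The formula and the simulation agree, and both named tests fail in the same way. The class-mean test holds its level here because the simulation contains no school-specific change.

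**7. School level.** Two schools leave 1 degree of freedom (critical t = 12.7), so variance between schools in the amount of change cannot usefully be estimated. If an assumed school ICC of change of 0.01 is added to a class ICC of 0.05 (10 to 20 students per class), an unstratified class-mean t-test rejects 8-12% of the time. Clustering by class therefore supports inference about these two schools only.

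**The case against.** The tests are given as examples, in a journal article, and any separate analysis plan is not shown. A cluster-aware method is therefore not excluded. That stands, and it is wrong to say that the plan is locked to these tests. But the examples are more than silence: they are the only methods named, the choice between them rests on distribution alone, and both are unsuitable if changes correlate within classes.

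The size depends on an ICC that the documents do not give. This stands in full. If the ICC of change is near zero, the named tests are nearly correct.

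With no control group, a valid p-value for a pre-post change would still not show an intervention effect, and the Discussion already urges caution on that ground. This is true and limits the importance of the point. The caution concerns missing control and generalisability, however, and does not correct the stated precision.

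Three stronger readings are not supported:
- **That the decision to progress rests on invalid tests.** The potential-effectiveness criteria in Table 3 ask for improvement or reduction, with no p-value or interval threshold. Clustering does not alter the observed mean change of the analysed students.
- **That the ideation regressions are shown to have the same fault.** The article gives no model or error structure for them. One can only ask that the clustering be carried through.
- **That the plan withholds the ICC a cluster-randomised trial needs.** The article mentions a randomised controlled trial only as an example and does not say what would be randomised. Nothing stops the team from estimating an ICC from the same data.

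**Conclusion.** The point holds in a limited form. The named tests assume independent changes where the delivery makes class correlation plausible, and the document offers no allowance for it. If the class ICC of change is positive, intervals and p-values are too favourable. At 385 students in 12 to 16 classes, standard errors are too small by a factor of about 1.1 at an assumed ICC of 0.01 and about 1.5 to 1.6 at 0.05. The direction follows from the design; the size rests on the assumed ICC, on the typical class numbers in the article and on reaching the target sample.

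The consequence is overstated precision of potential effectiveness in a pilot that feeds the planning of the next trial. It is not an invalid go or no-go rule. The change is worth making because it is cheap, and Study status says that the analysis is still under way.

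**What to change.** Name an analysis of pre-post change with class as the cluster. Either of these will do:

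- **Mixed model** on the repeated student outcomes: fixed effects for time, school and school-by-time; a random intercept for student; random effects for class and class-by-time; small-sample degrees of freedom. The school-by-time term is needed because a school main effect captures only level, not school-specific change.
- **Class summaries:** the mean change per class, analysed with stratification by school, on 12 − 2 = 10 to 16 − 2 = 14 degrees of freedom.

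For skewed outcomes, use a transformation or a bootstrap that resamples whole classes within school, in place of the signed-rank test. State that inference is conditional on these two schools. Report the class ICC of change with its confidence interval for each behavioural outcome. Use class-clustered errors in the ideation regressions, with a small-sample correction because there are few classes.

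The cost is somewhat wider intervals and a little more analysis work. No new measurements are needed, but a class identifier must be kept in the coded data. The class-level feedback in Table 2 suggests that class membership was known at baseline; the article does not say whether it survives in the delinked data set, so this should be checked first.

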## Dissemination strategy

Findings from this study will be disseminated to key stakeholders, such as MOE, HPB, the schools, and the parents of children who participated in the study. Findings from this study will be disseminated through at least two publications and will form part of the theses for a PhD student and a Master’s student. The improved version of intervention materials will also be shared with MOE for use as future resources for health education lessons.

## Discussion

Multiple health promotion programmes have been conducted in local public schools to improve children’s diet and movement behaviours; however, these interventions tend to be of a single component [14, 21]. With the growing body of literature demonstrating the effectiveness of multicomponent interventions, there is a need for multicomponent interventions to support healthy behaviour change among children in Singapore. However, information on the feasibility and acceptability of multicomponent interventions in Singapore is lacking. To our knowledge, this is the first study detailing the development and testing of a theory-driven multicomponent and school-based educational intervention among primary school children that targets both dietary and movement behaviours of children on the individual, interpersonal and environmental levels.

This study seeks to identify probable “active ingredients” of the intervention and understand the factors leading to a successful implementation of a multicomponent school-based intervention through the pilot testing of the PEDAL intervention. However, it should be noted that only two schools were recruited for the feasibility and pilot testing phase of the study which means that the findings may not be generalisable to all schools in Singapore or all co-educational public schools. As funding and resource constraints limited our ability to recruit more schools, only two schools underwent the intervention, and a pretest-posttest design was used. A limitation of such design is that it limits our certainty of how the outcomes might change in the absence of the intervention. Therefore, findings on the potential effectiveness should be interpreted with caution, and a larger-scale definitive trial (e.g. a randomised controlled trial (RCT)) should be conducted to assess the effectiveness of this intervention.

## Study status

The study is prospectively registered with the ISRCTN registry (ISRCTN16114046). The development of PEDAL commenced in April 2021, and the prototype was developed in December 2021 before feasibility was examined (Phase 2). Phase 2 was completed in November 2022, and the manuscript is currently being prepared for submission. The intervention materials were refined in December 2022 for the pilot test (Phase 3). The pilot intervention was completed in November 2023, and data analysis is underway.

## Data Availability

The datasets generated during and/or analysed during the current study will be available upon request from [name] after publication.
